#### Study procedure

*Baseline assessment*. Basic demographic and treatment information will be collected through an electronic medical record system. Our study will gather self-reported demographic information, including age, sex, marital status, education level, etc. We will obtain surgery and treatment information, including surgery date, surgery type (axillary lymph node dissection or sentinel lymph node dissection), the total number of dissected lymph nodes, chemotherapy regimen, radiotherapy regimen, and cycle number of treatment (chemotherapy/radiotherapy).

*Ongoing assessment*. Table 1 shows the standard assessment process of the follow-up assessment of our study. Clinical evaluations will include evaluations of BCRL, RBC, and depression. At each follow-up visit, patients will receive an upper-limb volume assessment and physical and imaging examination [16]. The research nurse will help them complete the Beck Depression Inventory-II questionnaire about patients’ mental status.

**Table 1 pone.0285772.t001:** The standard assessment process in cohort study—time points and primary outcomes.

Time point	BMI	Patients with secondary lymphedema or not	Patients with oncology recurrence or not	Beck Depression Inventory II	Medicine cost
**Perioperative stage**					
before surgery	√	/	/	√	√
**Chemotherapy therapy stage**					
circle 1	√	√	√	√	√
circle 2	√	√	√	√	√
circle 3	√	√	√	√	√
circle(4.5.6 …n- 1)	√	√	√	√	√
circle(n)—last circle	√	√	√	√	√
**Radiation therapy stage**					
before radiation therapy	√	√	√	√	√
after radiation therapy	√	√	√	√	√
**Follow-up stage**					
9th month(after surgery)	√	√	√	√	√
1st year(after surgery)	√	√	√	√	√
15th month(after surgery)	√	√	√	√	√
18th month(after surgery)	√	√	√	√	√
21th month(after surgery)	√	√	√	√	√
2nd years(after surgery)	√	√	√	√	√
27th month(after surgery)	√	√	√	√	√
30th month(after surgery)	√	√	√	√	√
33th month(after surgery)	√	√	√	√	√
3rd year(after surgery)	√	√	√	√	√

#### Diagnosis standards

Diagnosis of BCRL: We used a 200 ml limb volume difference as the diagnostic standard. The 200 ml limb volume difference standard is a universal criterion recommended by the 2020 Consensus Document of the International Society of Lymphology [2]. The limb volume difference will be measured with a Perometer device(an automated optoelectronic measurement of arm circumferences) [17].

Diagnosis of RBC: Physical examination and magnetic resonance imaging (MRI) for screening surveillance of breast cancer survivors. Breast cancer survivors who had biopsy-proven recurrence of breast cancer at presentation documented by fine-needle aspiration biopsy or core needle biopsy [18–21].

Diagnosis of depression: The screening tool will be the Beck Depression Inventory-II. We used the Beck Depression Inventory-II rubric; The scores are subdivided into the following grades: minimal(0–13 points), mild(14–19 points), moderate(20–28 points), and severe (greater than 29 points) [22, 23].

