## Patients and methods

This study is a prospective cohort study of breast cancer survivors. This study aimed to investigate and evaluate the incidence and correlation of BCRL, BCR, and depression. The primary outcome measures include the incidence and correlation of BCRL and BCR within three years. Choice of the time frame because three years is a high-incidence period of BCRL and BCR. The secondary outcome is depression.

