### Study sample

We will conduct a prospective cohort study of females with unilateral breast cancer in West China Hospital. We will recruit breast cancer patients between the ages of 18 and 55 years who will receive unilateral radical mastectomy or modified radical mastectomy, postoperative chemotherapy, and radiotherapy. Patients with breast cancer will be the first breast cancer diagnosed in West China Hospital, and the data on surgery and treatment will be extracted from the electronic medical record system. This cohort study will commence one week before breast cancer surgery and conclude after the three-year follow-up period.

Our study will need 1557 preoperative patients with a first-time invasive breast cancer diagnosis. Patients must meet the following criteria for inclusion.

Female subjects with ages older than 18 years and less than 55 years.Understand and sign the informed consent.Recruited in West China Hospital.First diagnosis of invasive breast cancer.Breast cancer patients will receive either radical or modified radical mastectomy.

There are four exclusion criteria; they are described briefly below.

Patients with bilateral breast cancerPatients had previously received neoadjuvant radiotherapy treatment before.Patients could not complete all the treatments and 3-year follow-up.There is significant asymmetry in the size of the upper extremities.The patients had cardiac dysfunction or renal and hepatic insufficiency.

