#### First stage—perioperative stage

Data will be collected at the time of the perioperative stage, including demographic data (sex, age, race, ethnicity, marital status, socioeconomic status, educational status, and BMI), clinicopathological factors (pathological type, breast cancer location, TNM staging, and comorbidities), surgery information (date of diagnosis, date of surgery, type of surgery, type of surgical incision, lymph node management, the total number of dissected lymph nodes), and baseline information (upper-limb volume difference, scale results of Beck Depression Inventory-II). Patient information in the perioperative stage will be collected through the electronic medical record after obtaining written informed consent. We will manage to build a follow-up database preoperatively. We will use this follow-up database for baseline and data collection, transfer, and storage.

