#### Secondary stage—chemotherapy therapy stage

Data will be collected at the time of the chemotherapy therapy stage, including the number of chemotherapy cycles, body mass index (BMI), upper limb volume measurement, assessment of tumor recurrence, and scale results of the Beck Depression Inventory-II. Once they receive the first round of chemotherapy, participants will be followed up in a regular oncology ward each cycle. Data collectors will conduct breast cancer-related lymphedema surveillance through upper-limb volume measurements. For patients who increase the upper-limb volume difference by more than 200 ml, secondary lymphedema is confirmed and diagnosed by a physician and physical therapist. Data will be collected at the time of the radiation therapy stage including the total number of radiation therapy cycles, body mass index (BMI), upper limb volume measurement, assessment of tumor recurrence, and scale results of the Beck Depression Inventory-II.

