**Perioperative stage**	
Demographic data	gender, age, race, ethnicity, marital status, socioeconomic status, educational status and body mass index (BMI)
Clinicopathological factors	pathological type, breast cancer location, TNM staging and comorbidities
Surgery information	date of diagnosis, date of surgery, type of surgery, type of surgical incision, Lymph node management, the total number of dissected lymph nodes
Baseline information	arm circumferences, scale results of Beck Depression Inventory-II
Financial information	treatment related cost

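### BCRL, a primary outcome and the grouping variable for every analysis, is defined once as a 200 ml difference between arms and once as an increase of more than 200 ml in that difference, and the protocol does not say which definition is analysed.

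*Protocol article*

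**What the plan says.** **Rule A, absolute difference (Diagnosis standards).** "We used a 200 ml limb volume difference as the diagnostic standard". No baseline value enters, and the text does not say whether exactly 200 ml counts. The device is named there too: "The limb volume difference will be measured with a Perometer device(an automated optoelectronic measurement of arm circumferences".

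**Rule B, increase in the difference (chemotherapy-stage section).** "For patients who increase the upper-limb volume difference by more than 200 ml, secondary lymphedema is confirmed and diagnosed by a physician and physical therapist". The inequality is strict and clinician confirmation is added, but no reference visit is named. The wording appears only in this stage's text.

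**Baseline arm measure.** The perioperative-stage text lists "baseline information (upper-limb volume difference, scale results of Beck Depression Inventory-II". The perioperative block of Table 2 lists "arm circumferences, scale results of Beck Depression Inventory-II". The later blocks of Table 2 list arm volume measurement.

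**Asymmetry.** Study sample excludes a woman if "There is significant asymmetry in the size of the upper extremities". No limit in ml or per cent is given.

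**Role of BCRL.** "The primary outcome measures include the incidence and correlation of BCRL and BCR within three years". Under Statistical analyses, lymphedema status also divides participants into two groups for every analysis and is a predictor in the logistic model for recurrence.

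**The concern.** A current difference between arms and a rise in that difference are different quantities. They coincide only if the arms had equal volume before surgery. For any other woman whose value lies near 200 ml, the two rules can give opposite answers.

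The variable is central to the study. It supplies a primary incidence, the two comparison groups and the exposure in the recurrence model, and its planning rate appears to drive the sample size. If the rule is left open, incidence and group membership can depend on which section an analyst follows, and the choice could be made after the data are seen. An article may leave detail to a fuller plan, but this is two conflicting statements of one endpoint, not an omission.

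**Working it through.** **1. The plan's own figure.** The Sample size calculation section gives N = z²p(1−p)/d² with d = 0.02, and inflates for 10% dropout. Alpha is not stated; two-sided 0.05 is assumed (z = 1.96).

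- BCRL, p = 0.1757: 3.8415 × 0.14483 / 0.0004 = 1390.9, so 1391; 1391/0.9 = 1546.
- Recurrence, p = 0.1553: 3.8415 × 0.13118 / 0.0004 = 1259.8, so 1260; 1260/0.9 = 1400.

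The stated 1557 is within 0.7% of the first figure and well away from the second, so the sample size evidently rests on the BCRL rate. Choosing one rule does not in itself change 1557.

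**2. The rules side by side.** Let b be the pre-surgery difference (affected minus unaffected arm) and c the change since then. Rule A is b + c beyond 200 ml. Rule B, if the reference is the pre-surgery visit, is c > 200 ml.

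| b (ml) | c (ml) | b + c (ml) | Rule A | Rule B |
|---|---|---|---|---|
| +80 | 130 | 210 | case | not a case |
| −80 | 240 | 160 | not a case | case |
| 0 | 210 | 210 | case | case |

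**3. Illustrative size.** The documents give no distribution for b or c, so every input here is an assumption except 17.57%. The protocol does not say which rule produced that rate; here it is assigned to rule B.

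- b is normal, mean 0, SD 25, 50, 75 or 100 ml, truncated at an assumed exclusion cut of 50, 100 or 200 ml.
- c is normal with SD 120 or 150 ml and mean 200 − 0.932 × SD (88 or 60 ml), so that P(c > 200) = 0.1757.
- For a given b, P(A) = P(c > 200 − b). Disagreement is |P(A) − 0.1757| averaged over b.

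| Baseline SD, cut (ml) | Rules disagree (change SD 150; 120) | Rule A incidence (change SD 150; 120) |
|---|---|---|
| 25, 50 | 3.1%; 3.9% | 17.8%; 18.0% |
| 75, 50 | 4.2%; 5.2% | 18.0%; 18.2% |
| 75, 100 | 7.4%; 9.2% | 18.9%; 19.6% |
| 75, 200 | 10.0%; 12.3% | 20.1%; 21.3% |
| 100, 200 | 12.2%; 15.0% | 21.2%; 22.8% |

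Over the whole grid, disagreement is about 3–15% and signed rule A incidence about 18–23%, against 17.57% under rule B. The incidence gap is 0.3 to 5.2 percentage points. It exceeds the protocol's 2% permissible error in 6 of the 24 settings, all with baseline SD of 75 ml or more and a cut of 100 ml or more.

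**4. Dependence on the anchor.** If 17.57% is assigned to rule A instead (baseline SD 75 ml, cut 200 ml), rule B incidence is about 14–15% and disagreement 9–11%.

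**The case against.** **The second rule may be loose wording.** It sits in one stage's procedures, names no reference visit, and may simply mean a difference above 200 ml. That is possible. However, the Introduction justifies the cohort by a limb baseline and the tracking of changes, and the perioperative stage collects a volume difference that rule A never uses. A reader cannot tell which is meant, so the text needs settling on either reading.

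**The exclusion of asymmetric arms limits the problem.** This stands in part. As baseline differences approach zero the rules converge, and a tight cut brings disagreement down to about 3–5%. Without a threshold, the amount of asymmetry left cannot be known.

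**The figures are not from the documents.** This stands. The illustration also treats one visit and a mechanical cut, whereas BCRL is assessed repeatedly and rule B adds clinician confirmation.

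**Stronger readings that the documents do not support.**

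- A reader might infer two different baseline measurements. The Perometer is itself described as measuring arm circumferences to obtain the volume difference, so the two labels may describe one measurement. This is a wording mismatch.
- A reader might infer that women with asymmetric arms are misclassified. The text shows only that they can be classified differently; neither rule is fixed as the reference.
- A reader might infer that every association is diluted. That would need non-differential error, which cannot be established from the protocol.

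**Conclusion.** The contradiction is real, can be read directly from the text, and concerns a rule on which every analysis depends. Nothing in the article says which definition sets the primary outcome or the groups, which visit an increase is measured from, or how much baseline asymmetry is allowed. Women with remaining asymmetry can therefore change group according to the rule used.

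That conclusion needs no simulation. The 3–15% disagreement and the 18–23% incidence are illustrations under assumed normal distributions, an assumed exclusion cut and an assumed anchor for 17.57%. They show that the choice may matter against a 2% error margin, not that it will.

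**What to change.** - Reconcile Diagnosis standards and the chemotherapy-stage section into one analysis-endpoint rule. State the quantity, the reference visit, the inequality and whether clinician confirmation is part of the endpoint, and apply the rule at every visit.
- Either rule used consistently removes the contradiction. Because a pre-surgery volume difference is already planned, the change from that value in affected minus unaffected arm volume can serve as the analysis endpoint, with the other rule reported as a sensitivity analysis.
- State the threshold that the asymmetry exclusion uses, and which rule produced the 17.57% planning rate.
- Align the baseline label in Table 2 with the volume difference named in the perioperative-stage text.

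The cost is wording in these sections; no measurement is added beyond the planned baseline volume difference. The change concerns the analysis endpoint only and leaves diagnosis for patient care as it is.

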## Introduction

Breast cancer-related lymphedema (BCRL) is closely related to a high risk of cancer-related treatment, breast cancer recurrence, and disability [1]. In breast cancer patients, secondary lymphedema is a symptom cluster encompassing progressive upper-limb swelling, skin changes, limb numbness, pain and discomfort, restricted range of motion, and nonpitting edema [2]. These would decrease physical and mental function, increase disease burden and increase financial costs. It is a common complication in breast cancer patients [3–6]. Considering the establishment of a baseline of the upper limb and tracking changes, a screening cohort of secondary lymphedema may be the optimal solution to develop screening programs and evaluate the prevalence of breast cancer-related lymphedema in China.

Breast cancer recurrence (BCR) is a negative outcome in patients with breast cancer after either mastectomy or breast-conserving therapy (BCT) [7]. Breast cancer can recur locally, regionally, and/or at distant metastatic sites [8]. It is a hammer blow for breast cancer survivors [9]. It directly threatens breast cancer survivors’ life expectancy and decreases their quality of life. BCRL and BCR share risk factors such as higher BMI, pathological type, breast cancer location, tumor node metastasis(TNM) staging and comorbidities, and treatment-related factors (surgery, radiotherapy, and chemotherapy) [10]. Early detection helps implement personal and precise medical precautions for patients with secondary lymphedema (or breast cancer recurrence).

Up to 30% of breast cancer survivors have depressive symptoms [11]. Depressive affect includes emotional lability, irritability, and social withdrawal [12]. Depression is an emotional difficulty associated with an increased disease burden and treatment-related cost and a decreased ability to cope with breast cancer. Fear of cancer recurrence also directly affects mental health, especially anxiety and depression [13].

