### Statistical analyses

The following primary factors will be calculated when each of the study stages (perioperative stage, chemotherapy therapy stage, radiation therapy stage, follow-up stage) is completed: BCRL incidence, RBC rate, and incidence of depression. To calculate the incidence of the primary outcomes, we will sum the total of participants within each of the stages as the denominator and sum the total of people with one of the primary outcomes as the numerator. For every statistical analysis, the participants will be classified into two groups based on whether they developed secondary lymphedema. Incidence rates of breast cancer recurrence and depression will be calculated separately for groups. The chi-square test will be used to compare the rates rate between the two groups [26]. As a secondary outcome, depression symptoms will be repeatedly measured in this study. The results of the assessment of depression symptoms will be compared across periods and between treatment-related events using statistical analysis with repeated measures analysis of variance (ANOVA).

We will identify clinicopathological factors, surgery information, lymph node management, breast cancer-related treatment, and body mass index(BMI) as risk factors due to their reported associations with secondary lymphedema, recurrence of breast cancer, and depression symptoms. Multivariate logistic regression will be used to determine whether secondary lymphedema and other parameters can predict breast cancer recurrence. To assess the correlates with these risk factors and outcomes, we will describe the strength of the association using clinically meaningful and statistically significant effect sizes, and a correction will be based on demographic characteristics.

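### The stage-wise depression incidence does not set aside women already depressed before surgery, so it is a prevalence, and no BDI-II score is named as a case

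*Protocol article*

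**What the plan says.** Under Diagnosis standards, lymphedema and recurrence each have a criterion that yields a yes or no: a 200 ml limb volume difference and biopsy proof. The depression entry reads "Diagnosis of depression: The screening tool will be the Beck Depression Inventory-II". Four grades follow: minimal for scores 0–13, mild for 14–19, moderate for 20–28, and a top grade worded "severe (greater than 29 points". No grade or score is said to count as depression.

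The Statistical analyses section lists three quantities, "BCRL incidence, RBC rate, and incidence of depression", to be calculated "when each of the study stages (perioperative stage, chemotherapy therapy stage, radiation therapy stage, follow-up stage) is completed". The rule for each rate is this: "sum the total of participants within each of the stages as the denominator and sum the total of people with one of the primary outcomes". The second of these totals is the numerator. The section adds: "Incidence rates of breast cancer recurrence and depression will be calculated separately for groups". The groups are women who did and did not develop lymphedema, and the test is chi-square. Separately, depression symptoms are to be analysed over time by repeated measures ANOVA.

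In Table 1, the row before surgery has a tick for the BDI-II and a slash for lymphedema and for recurrence. The exclusion criteria under Study sample do not mention depression. The Record section says onset and diagnosis times will be noted.

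**The concern.** Incidence counts new cases among people who were free of the condition at the start. The stated rule restricts neither the numerator nor the denominator in that way. For lymphedema and recurrence this does little harm, because patients are recruited before surgery for a first cancer and significant limb asymmetry is an exclusion. Depression has no such safeguard, and some women may already be depressed when they enter.

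The lymphedema comparison is at stake. Depression present before surgery comes before any lymphedema and cannot result from it, yet those cases enter the chi-square test. They can dilute a real difference in new depression or, if the groups differ at baseline, produce a difference that new depression does not explain. A binary rate also needs a case definition, and the grades leave three candidates: mild or worse, moderate or worse, or severe alone.

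**Working it through.** **The article's own figure.** It computes no depression rate. Its only computed figure is the sample size. With p = 0.1757, d = 0.02 and two-sided alpha 0.05 (assumed, as none is stated): 1.96² × 0.1757 × 0.8243 / 0.02² = 1390.9, so 1391. Then 1391 / 0.90 = 1545.6, so 1546, within 0.7% of the stated 1557. Depression plays no part in this figure, so the sample size is unaffected. I use 1557 below only as a denominator.

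**Grades.** The intervals are 0–13, 14–19, 20–28 and above 29. Of the integer scores, only 29 falls in none. If a case is 14 or more, or 20 or more, a score of 29 is a case whichever neighbouring grade it joins. The gap changes the rate only if severe alone defines a case.

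**The perioperative stage.** The only BDI-II that Table 1 places in this stage is taken before surgery. Cases over all participants at that point can only be a baseline prevalence.

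**Later stages.** Let b be the proportion depressed before surgery and i the new-onset risk among the rest. If baseline cases still count, the rate as written is b + i(1 − b), against a true incidence of i.

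No baseline rate is given. The only frequency is in the Introduction, "Up to 30% of breast cancer survivors have depressive symptoms". It is a ceiling and refers to survivors, so I use it only as the top of an assumed range. The values of i are also assumed.

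| b | i = 5% | i = 10% | i = 20% | women at risk, 1557 × (1 − b) |
|---|---|---|---|---|
| 5% | 9.75% | 14.5% | 24% | 1479 |
| 10% | 14.5% | 19% | 28% | 1401 |
| 20% | 24% | 28% | 36% | 1246 |
| 30% | 33.5% | 37% | 44% | 1090 |

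The excess over i is b(1 − i), which is always upward when baseline cases persist. If only a share r of them still counts, the excess is b(r − i), which is smaller and stays upward while r exceeds i.

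**Removing baseline cases from the numerator only.** With all participants still as the denominator, the rate is i(1 − b). At b = 30% and i = 10% this is 7%, now too low. The denominator also has to change.

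**The lymphedema comparison.** With the same b in both groups, the difference shrinks by the factor (1 − b). For example, at b = 30%, assumed new onset of 25% v 15% becomes 47.5% v 40.5%, which is 7 points instead of 10. With unequal b and the same i = 10%, baselines of 20% v 10% give 28% v 19%, a 9-point difference with none in new onset.

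**The case against.** Several points on the other side are fair.

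- **The symptom analysis.** A reader might infer that the whole secondary outcome is compromised. It is not. The analysis that the article introduces as the secondary-outcome analysis is the repeated measures ANOVA. Run on BDI-II scores, it needs no cut-off, is untouched by the gap at 29 and can use the pre-surgery score. This stands.
- **The gap at 29.** It looks striking but is minor, as shown above. Nor does the article show which neighbouring grade 29 belongs to. This stands.
- **An unseen analysis plan.** A dichotomisation rule is often left there, and nothing shows that a cut would be chosen after seeing the data. The second half stands. The first is weaker, because the article has a diagnosis section that settles the other two outcomes and, for depression, supplies only grades.
- **Ambiguous wording.** The numerator refers to primary outcomes, while the opening of Patients and methods makes depression secondary. But the preceding sentence in Statistical analyses lists depression among the primary factors to be calculated, and no other rule for its rate is given.
- **Onset time is recorded.** New cases could therefore be separated, but no rule says they will be, and the stated denominator would still be wrong.
- **Direction of the group bias.** A reader might infer a false link between lymphedema and depression. With equal baselines the difference is diluted instead, and the article gives nothing to show imbalance. This stands.
- **Weight.** Depression is secondary, does not drive the sample size, and the Discussion calls the study explorative. That limits the importance of the defect without removing it.

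**Conclusion.** The point holds for the binary depression rate and its chi-square comparison. Followed as written, the plan labels a prevalence as incidence and carries pre-existing depression into the comparison by lymphedema. The missing case definition is part of the same defect, and the ungraded score of 29 is a minor addition.

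The size cannot be fixed from the article. Under the assumed ranges (5–30% depressed before surgery, 5–20% new onset, baseline cases persisting), the rate as written would be 9.75% to 44%, against a true 5–20%. No single value in that range should be quoted as the expected error. The documents do not support the wider readings that the score-based analysis is affected, that a cut-off will be chosen from the data, or that a spurious lymphedema effect is to be expected.

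**What to change.** - **Case threshold.** Name one of the existing band edges as the score that makes a case, before analysis.
- **Grades.** Reconcile the bands in Diagnosis standards with the rubric the article cites, so that every score has a grade.
- **Baseline.** Report pre-surgery depression as baseline prevalence, and do not call the perioperative figure an incidence.
- **Incidence.** Calculate it, and compare the lymphedema groups, only among women below the threshold before surgery. Alternatively, keep all participants and label the stage rates as prevalence.
- **Adjustment.** Alongside the chi-square, fit a regression for depression adjusted for the pre-surgery BDI-II score.

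It may be tempting to count only depression that arises after lymphedema. That should not be done as a simple rule, because women without lymphedema would have no matching start time. It needs lymphedema handled as a time-dependent exposure or a landmark analysis.

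**Cost.** A few sentences, one extra model and no new data, since the pre-surgery BDI-II is already collected. The incidence denominator becomes smaller: about 1479 to 1090 of 1557 at 5–30% baseline depression, before dropout. Women who leave it still contribute to the baseline prevalence and the repeated measures ANOVA.
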